## Abstract

**Background:**

South Africa bears a large HIV burden with 7.8 million people with HIV (PWH). However, due to suboptimal antiretroviral therapy (ART) adherence and retention in care, only 66% of PWH in South Africa are virally suppressed. Standard care only allows for suboptimal adherence detection when routine testing indicates unsuppressed virus. Several adherence interventions are known to improve HIV outcomes, yet few are implemented in routinely due to the resources required. Therefore, determining scalable evidence-based adherence support interventions for resource-limited settings (RLS) is a priority. The multiphase optimization strategy (MOST) framework allows for simultaneous evaluation of multiple intervention components and their interactions. We propose to use MOST to identify the intervention combination with the highest levels of efficacy and cost-effectiveness that is feasible and acceptable in primary care clinics in Cape Town.

**Methods:**

We will employ a fractional factorial design to identify the most promising intervention components for inclusion in a multi-component intervention package to be tested in a future randomized controlled trial**.** We will recruit 512 participants initiating ART between March 2022 and February 2024 in three Cape Town clinics and evaluate acceptability, feasibility, and cost-effectiveness of intervention combinations. Participants will be randomized to one of 16 conditions with different combinations of three adherence monitoring components: rapid outreach following (1) unsuppressed virus, (2) missed pharmacy refill collection, and/or (3) missed doses as detected by an electronic adherence monitoring device; and two adherence support components: (1) weekly check-in texts and (2) enhanced peer support. We will assess viral suppression (<50 copies/mL) at 24 months as the primary outcome; acceptability, feasibility, fidelity, and other implementation outcomes; and cost-effectiveness. We will use logistic regression models to estimate intervention effects with an intention-to-treat approach, employ descriptive statistics to assess implementation outcomes, and determine an optimal intervention package.

**Discussion:**

To our knowledge, ours will be the first study to use the MOST framework to determine the most effective combination of HIV adherence monitoring and support intervention components for implementation in clinics in a RLS. Our findings will provide direction for pragmatic, ongoing adherence support that will be key to ending the HIV epidemic.

**Trial registration:**

ClinicalTrials.gov NCT05040841. Registered on 10 September 2021.

**Supplementary Information:**

The online version contains supplementary material available at 10.1186/s13063-023-07322-z.

## Background

Advances in antiretroviral therapy (ART) have reduced illness and death for people with HIV (PWH), but major gaps in the care continuum persist. Sub-Saharan Africa is home to nearly 70% of the world’s PWH; South Africa, with 7.8 million PWH, bears the continent’s greatest HIV burden. By 2018, nearly five million PWH had accessed ART in South Africa, but weaknesses were clear: 17% of PWH who start ART fall out of care by 16 weeks and >20% are lost in the first year [1–3]. Adherence to ART in South Africa ranges from 40 to 75% [3–5], far below what experts believe is required for successful treatment (typically at least 80%, even with potent, modern regimens) [6–8]. Mainly due to suboptimal adherence and retention, only 51–86% of people show suppressed virus at 12 months [3, 4, 9–12]. Overall, approximately 66% of PWH are believed to be virally suppressed [13]. These outcomes predict higher mortality, more HIV transmission, and drug-resistant HIV, hindering the World Health Organization’s “End HIV/AIDS by 2030” goals [14].

Early detection of suboptimal adherence among PLW initiating ART, and linkage to support for these patients is critical. The evidence shows that people who miss doses early in treatment go on to miss clinic visits, exhibit poor outcomes, and be disproportionately lost to care [15–17]. Existing data from studies conducted in the City of Cape Town show that PWH with unsuppressed virus (>1000 copies/ml), potentially indicating suboptimal adherence, were more likely to be lost to care in later years than virally suppressed patients [18, 19]. Intervention studies provide ample evidence that patients can benefit from support interventions [20], including peer groups [21], motivational interviewing [21–23], and text message reminders [21, 23, 24]. In addition, there is evidence suggesting that multi-component interventions provide stronger support than single-component interventions [23, 25]. However, such interventions are often not implemented in routine care due to cost and resource requirements that influence systems of care. Moreover, people who will need extra support are not routinely identified at the time of ART initiation: a key challenge is that new patients may struggle and be lost to care before they are identified as being in need of support.

There are several methods of adherence monitoring and ways of identifying people who need extra support—each with its own strengths and weaknesses. The current standard for monitoring adherence in South Africa is through self-report, which is often unreliable [2], and through infrequent viral load measurements, recommended at 4 and 12 months after initiating ART and annually thereafter [26]. However, feedback of the viral load result to the patient is often only given at the next routine clinic visit, resulting in a delay in initiating adherence support measures. Electronic adherence monitors (EAM) that track adherence in real time are acceptable and feasible in many settings and have been used to deliver reminders and trigger just-in-time support [27–32]. In HIV treatment, the benefit-cost ratio of broad use of EAM in clinical settings is unknown. Another method that leverages existing infrastructure is pharmacy refill monitoring (PRM). PRM data can detect suboptimal adherence after a missed refill, prior to viral load becoming unsuppressed [2, 33]. A third approach is early patient outreach when unsuppressed virus is detected. Early outreach is not done in most resource-limited settings, but is feasible and well-liked by patients [34].

This study’s primary research goal is to identify the optimal combination of evidence-based and scalable HIV interventions for resource-limited, high-burden settings. In Cape Town, health officials have established Risk of Treatment Failure (ROTF) clinics, where patients with unsuppressed virus receive extra support via (a) one nurse-led counselling session and (b) peer counselling (3–4 sessions) [35]. Our hypothesis is that the test we have designed will allow us to identify a superior combination of interventions. Thus, working in collaboration with the City of Cape Town, we plan to (1) test the relative contributions of five promising intervention components, three comprising adherence monitoring methods, and two comprising extra support elements; (2) collect cost and other implementation data; and (3) optimize a multi-component intervention package with high levels of cost-effectiveness and characteristics identified as necessary for implementation success.

The gold standard for testing interventions is the randomized controlled trial (RCT); however, when planning and testing an intervention with multiple components, paired comparisons of the individual elements is complicated and costly. A more efficient approach to developing a multi-component intervention is the novel multiphase optimization framework (MOST) [36, 37], an engineering-inspired framework for identifying the most efficacious combination of components that can then be included in a “packaged” or multi-component intervention. In this study, SUSTAIN (Supporting Sustained HIV Treatment Adherence after Initiation), we will employ a MOST framework to determine the combination of interventions—with the highest levels of efficacy and cost-effectiveness and that are feasible and acceptable in primary care clinics—compared to standard of care.

## Methods

The study protocol has been reported in accordance with the Standard Protocol Items: Recommendation for Clinical Intervention Trials (SPIRIT) guidelines [38] (see Fig. 1 and Additional File 1 for details).

**Fig. 1 Fig1:**
[figure not shown]
Schedule of enrolment, interventions, and assessments

### Overview

MOST has three phases: (1) preparation; (2) optimization; and (3) evaluation [39]. The preparation phase involves the development of a conceptual framework, the identification of feasible candidate intervention components, and setting the optimization objective. In the optimization phase, comparative effectiveness of the individual components is assessed using one of several potential study designs and, finally, in the evaluation phase the optimized intervention package is assessed through an RCT.

#### Conceptual framework

Our overall study is informed and supported by an adapted version of the Self-Determination Theory (SDT). SDT posits that a person is motivated to alter behaviors when their needs for connectedness, efficacy, and autonomy have been satisfied (see Fig. 2) [40, 41]. We hypothesize that purposeful adherence monitoring and outreach when suboptimal adherence occurs, regardless of specific form of monitoring, will increase feelings of autonomy, prompting improved motivation and competence. We further hypothesize that active adherence monitoring alongside strengthened adherence support will increase patients’ appreciation for the value of adherence and retention and promote their competency. Finally, we adapted the model to include “social support” as a mediator to improve competency and adherence (as reflected in other social support theories and Social Cognitive Theory) [42, 43]. This adapted model also accounts for other major variables such as substance use, mental health, and stigma, which are known to influence ART outcomes directly and as moderating factors [44–49].

**Fig. 2 Fig2:**
[figure not shown]
Theoretical framework of the SUSTAIN study. Abbreviations. OTR, outreach. PRM, pharmacy refill monitoring. EAM, electronic adherence monitoring

Prior to beginning this study, the team carried out the preparation phase of MOST. We partnered with local officials and clinical staff in Cape Town to review evidence for adherence interventions and conduct formative research to identify the most effective, acceptable, and feasible intervention components for patients and providers. These components formed the basis for a pilot study [50] in which we used in-depth interviews (IDIs) with patients and focus groups with providers to determine the most preferred intervention components to advance to the next phase. For our final study design for the optimization phase, we incorporated the two most preferred support strategies identified in our pilot study: (a) weekly check-in texts (S1); and (b) enhanced peer support, using motivational interviewing (MI) (S2). We also included three means of rapidly identifying and reaching out to nonadherent patients: (1) Early call to the patient (e.g., within a week) after a standard viral load test showing an unsuppressed virus (M1); (2) patient pharmacy refill monitoring, with an early call to the patient after a missed refill (M2); and (3) real-time EAM, again with an early call to the patient if doses are missed (M3). These five intervention components are described in Table 1.

**Table 1 Tab1:** Intervention components

**Component**	**Component type**	**Frequency**	**Method of delivery**
Standard of Care (SoC): Informing the patient of the VL result at their next clinic visit and initiating counselling	SoC	At the next visit after month 4 and month 12 after ART initiation	In-person at the clinic
M1: Call to the patient after unsuppressed VL on routine testing	Adherence monitoring	At month 4 and month 12 after ART initiation	Direct phone calls
M2: Pharmacy refill monitoring and call to the patient	Adherence monitoring	Monthly or 2 monthly for 12 months, depending on clinic visit schedule	Direct phone calls
M3: Electronic adherence monitoring and call to the patient	Adherence monitoring	Reviewed weekly	Direct phone calls
S1: Weekly check-in text messages	Adherence support	Weekly for 12 weeks once suboptimal adherence detected	Automated weekly text messages with option to reply
S2: Peer support (Basic or enhanced)	Adherence support	Monthly for 3 months once suboptimal adherence detected	Basic: One-on-one or group adherence sessions delivered by clinic counsellors Enhanced: One-on-one motivational interviewing delivered by study staff

Abbreviations: *SoC*, standard of care; *VL*, viral load; *ART*, antiretroviral therapy

#### Setting the optimization objective

The optimization objective is to identify the combination of interventions with the greatest levels of efficacy (viral suppression and retention in care) and cost-effectiveness that are feasible and acceptable in primary health clinics supplying ART in resource-limited settings.

### Optimization phase

This phase of the study—SUSTAIN—involves a fractional factorial design and regression analysis adjusted for clustering by clinic to accomplish three aims: (1) to determine the relative efficacy of five intervention components on the primary and secondary outcomes (described below); (2) to assess implementation, service, and client outcomes pertinent to each intervention component; and (3) to model the multi-component intervention optimized for cost-effectiveness and implementation success.

#### Study setting

This study is taking place in three City of Cape Town clinics in the Klipfontein and Mitchell’s Plain health districts in South Africa. Each of these clinics serves a population with a high prevalence of HIV. Although precise numbers are not available, prevalence in these districts is believed to be higher than in Cape Town generally which was estimated to be 9.5% in 2017 [51]. Each clinic provides free ART services delivered by doctors, clinical nurse practitioners, and registered nurses [26].

#### Eligibility criteria

Study participants must be adolescents aged 16–17 years or adults ≥18 years of age, who are presenting to the clinic for initiation of ART. Study participants must be willing and able to sign informed consent or, in the case of minors, informed assent with parents willing to sign informed consent. They must have a working cellphone and be willing to receive study-related text messages. They must also be willing and able to comply with study procedures, including using an EAM and providing current contact information. We aim to enroll 512 participants (roughly 170 per clinic) between March 2022 and February 2024.

#### Recruitment

Participants will be recruited by community research workers who are embedded within the clinics and work closely with clinic staff who are initiating people on ART. Study leadership will evaluate enrollment rates on a monthly basis to identify if there is a need to adjust the recruitment strategy.

#### Informed consent

All potential participants in the trial will undergo informed consent procedures, including emphasis that participation is voluntary and that refusal will have no negative impacts on the ART service they receive at their clinic. Adult eligible participants aged 18 years and over who agree to enroll in the study will provide full written informed consent. Eligible adolescents of ages 16 and 17 years will not be able to enroll unless they are willing to complete an assent form and are able to bring a parent or guardian with them to complete a parental full informed consent document. All informed consent and assent processes will be conducted in the language of the participants choice (usually English or Xhosa); and the forms will be available in these languages as well. The informed consent and assent document will contain contact details for study staff who are available to answer questions about the study.

#### Timeline

Participants will be enrolled for a total of 24 months, with study follow-up visits at months 4, 8, 12, 18, and 24 (Fig. 1). The intervention components will be applied for the first 12 months of enrollment.

#### Intervention components

At enrollment, each participant will be issued an EAM to measure adherence over time, and for those assigned to M3, to actively monitor adherence. Enrolled participants will be randomized to one of 16 study conditions (i.e., combination of monitoring and intervention strategy—see Table 2). Four of the five intervention components (M1, M2, M3, & S1) can either be switched “on” (the component is applied) or switched “off” (the component is not applied). The counselling component (S2) can be either basic (standard of care) or enhanced (motivational interviewing). As this study includes only behavioral interventions, all routine medical care provided by the clinics will continue as needed. There is no prohibited concomitant care. While the study interventions monitor and promote adherence and retention in care, there are no additional measures to promote retention within the study itself (e.g., outreach to participants who have missed study visits), as these additional activities would influence retention in care as an outcome and undermine the assessment of our interventions.

**Table 2 Tab2:** Intervention components and study conditions in the fractional factorial design

**Study condition** **Intervention components**	1	2	3	4	5	6	7	8	9	10	11	12	13	14	15	16
Core (standard care): After a VL test shows unsuppressed virus, the patient is alerted at the next clinic visit and given a counselling session	X	X	X	X	X	X	X	X	X	X	X	X	X	X	X	X
M1. Call to the patient after VL test result of unsuppressed virus (M1/Call)	O	O	O	O	O	O	O	O	X	X	X	X	X	X	X	X
M2. Pharmacy refill monitoring + Call to the patient (M2/PRM)	O	O	O	O	X	X	X	X	O	O	O	O	X	X	X	X
M3. Electronic adherence monitoring + Call to the patient (M3/EAM)	O	O	X	X	O	O	X	X	O	O	X	X	O	O	X	X
S1. Weekly check-in text messages (S1/Text)	O	X	O	X	O	X	O	X	O	X	O	X	O	X	O	X
S2. Peer support counselling: Basic (B) or Enhanced (E) (S2/Peer)	E	B	B	E	B	E	E	B	B	E	E	B	E	B	B	E

Abbreviations: *VL*, viral load; *PRM*, pharmacy refill monitoring; *EAM*, electronic adherence monitoring

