#### Outcome measures

We will be collecting data using viral load results (at month 4 and month 12—obtained from patient records and the National Health Laboratory Service online system), EAMs (daily), pharmacy refills (monthly), and participant and staff surveys. The primary outcome will be viral suppression at month 24 post-enrollment as measured by plasma HIV-1 viral load <50 copies/mL. Secondary outcomes will include viral suppression at month 12, change in viral load over time, and total days of unsuppressed virus during study participation. Additional secondary outcomes include the following: mean electronic adherence and percent of participants ≥90% and ≥80% adherence in months 12 and 24; mean adherence over months 1–12 and 1–24; retention in ART care (percent of participants attending all refill visits within 7 days for monthly refills and 14 days for longer refill intervals) over months 1–12 and 1–24; percent of participants attending ≥75% refill visits (within 7 days), over months 1–12 and 1–24; percent of participants lost to care, defined as no clinic contact for ≥12 weeks at month 24); and time to suboptimal adherence detection and linkage to support (number of days from month 0 to day identified as nonadherent, as per the definition used in their intervention; number of days from month 0 to linkage to ROTF support).

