#### Data and statistical analysis

Study staff will collect data directly onto the REDCap database using password-protected tablets. The REDCap database was designed with automated internal checks to ensure data entered are accurate and complete. In addition, the site follows a data management plan, which outlines quality control and quality assurance practices. All participants will be assigned a study identifier and data for analysis will only be identified through this number. All documents that contain personal identifiers will be kept in locked cabinets with limited access.

We will employ a series of descriptive and inferential statistical methods and techniques for data analysis. For dataset preparation, missing baseline data on socio-demographics will be imputed using a single imputation technique if the proportion missing is <10% or using a multiple imputation technique if the proportion missing is ≥10%, respectively. In cases of missing viral load data, we will treat the result as detectable, in accordance with our primary intention-to-treat (ITT) analytic approach, similar to other studies [3, 63]. For missing adherence data, the most recent month’s adherence will be used to estimate single-month adherence; for cumulative calculations, available data over the period will be used.

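### Electronic adherence in months 1–12 is scored from the record that triggers M3 calls, so the M3 contrast cannot separate better pill-taking from better device use

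*Protocol article*

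**What the plan says.** All from the Protocol article.

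- **One device, two uses.** Intervention components: "each participant will be issued an EAM to measure adherence over time, and for those assigned to M3, to actively monitor adherence".
- **The trigger.** The text after Fig. 2 describes M3 as "real-time EAM, again with an early call to the patient if doses are missed". The Abstract's Methods paragraph says that the outreach follows "missed doses as detected by an electronic adherence monitoring device". Table 1 gives a weekly review for M3.
- **The call period.** Timeline: "The intervention components will be applied for the first 12 months of enrollment".
- **The outcomes.** Outcome measures lists as secondary "mean electronic adherence and percent of participants ≥90% and ≥80% adherence in months 12 and 24; mean adherence over months 1–12 and 1–24". The sources named beside viral load are "EAMs (daily), pharmacy refills (monthly), and participant and staff surveys", so the device is the only daily source.
- **Missing adherence data.** Data and statistical analysis fills a missing single month from the most recent month. It adds that "for cumulative calculations, available data over the period will be used".
- **Efficacy for optimisation.** Setting the optimization objective defines efficacy as viral suppression and retention in care. Electronic adherence is not named there.

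**The concern.** While M3 is active, study staff act on gaps in the outcome record at one level of M3 and not at the other. A call about a gap may restore pill-taking, or it may only restore use of the device, and the recorded score rises in both cases. Randomisation does not remove such an effect, because it arises after allocation and depends on it. Issuing the device to everyone equalises possession but not follow-up of its record.

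The article applies this kind of care elsewhere. Under Intervention components it declines outreach after missed study visits, because that would act on retention as an outcome. It does not discuss the parallel issue for the device.

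At stake is the reading of M3 on month-12 electronic adherence (mean, ≥80% and ≥90%), on mean adherence over months 1–12, and on the first half of months 1–24. Optimization phase, aim 1, covers component effects on secondary as well as primary outcomes, so these contrasts will be estimated. The Discussion places EAM at the complex end of the three monitoring methods.

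**Working it through.** **1. Does the outcome window overlap the call period?**

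| Outcome | M3 calls active? | Scored from the device? |
|---|---|---|
| Electronic adherence, month 12 | Yes | Yes |
| Mean adherence, months 1–12 | Throughout | Yes |
| Mean adherence, months 1–24 | First half | Yes |
| Electronic adherence, month 24 | No, ended 12 months before | Yes |
| Viral load outcomes | – | No |
| Refill-based retention | – | No |

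**2. The one stated figure for this outcome.** Sample size says that differences of 11–15 points in ≥90% adherence are detectable. It gives no baseline rate. At two-sided 0.05 and 80% power, for assumed baselines of 40–75%, the minimum detectable difference is 9.9–12.4 points at 256 per level and 10.5–13.1 at 229 per level. The lower part of the stated range is matched. The upper end cannot be checked without the missing inputs. The point here does not depend on it.

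**3. Size for mean adherence.** M3 is on in 8 of 16 conditions of 32 participants (Table 2; Randomization): 8 × 32 = 256 v 256. Everything else is assumed, because the article gives no data: true adherence 80% at both levels, the device registers 90% of taken doses with M3 off, unregistered doses are scored as missed, and the SD is 25 points.

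Recorded adherence = true adherence × share of taken doses registered.

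- M3 off: 0.80 × 0.90 = 72.0%.
- M3 on, capture 95%: 0.80 × 0.95 = 76.0%, a spurious 4.0 points.
- M3 on, capture 92%: 0.80 × 0.92 = 73.6%, a spurious 1.6 points.
- M3 on, capture 91%: 0.80 × 0.91 = 72.8%, a spurious 0.8 points.

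SE = 25 × √(2/256) = 2.21. Probability that a nominal two-sided 5% test rejects:

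- 4.0/2.21 = 1.81; P(Z > 1.96 − 1.81) = 0.44.
- 1.6/2.21 = 0.72; 0.108 + 0.004 = 0.11.
- 0.8/2.21 = 0.36; 0.055 + 0.010 = 0.065.

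With SD 20 to 30, the first becomes 62% to 33% and the second 15% to 9%.

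**4. Threshold outcomes.** I simulated a 30-day month with identical pill-taking at both levels (beta-distributed, mean 80%, SD 25 points). Capture of 90% v 95% moves the proportion at ≥90% from about 28% to 45%, a spurious 17 points. For true means of 75–85% and SD 20–25 the shift is 11–21 points. Capture of 90% v 92% gives about 7 points and rejection slightly above 40%. The ≥80% outcome moves by 7 points (90% v 95%) under the same model, with rejection of about 37%, which is no more sensitive than the mean. The added sensitivity thus lies mainly at ≥90% and depends on the assumed distribution.

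**The case against.** The strongest reply has five parts.

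- **The mechanism is inferred.** The article does not say how the device works or that calls discuss its use. This stands. A reader might infer that the M3 contrast is biased by a known amount. The documents support only a risk, and its size is unknown. If capture differs by 1 point, the test on the mean is close to nominal (6.5%).
- **A gap need not count as a missed dose.** A reader might infer that every device gap is scored as non-adherence. The missing-data rule may instead treat some gaps as missing. This stands too, and how the two are told apart may be set out in the full protocol or analysis plan. It limits the size of the problem but does not remove it, because a dose taken without the device may still look like a missed dose.
- **The optimised package is chosen on other outcomes.** A reader might infer that this artefact would carry M3 into the package. The optimization objective names viral suppression and retention, and neither comes from the device. This stands, and it confines the point to secondary outcomes.
- **The other components are not wholly separate.** Under Table 1, S1 and S2 start once suboptimal adherence is detected, and in M3-on conditions the device record may be what detects it. This stands and needs a note, although the differential handling of the record is between levels of M3.
- **Much of the remedy is already planned.** Month-24 electronic adherence and viral suppression at months 12 and 24 are listed outcomes. This is correct. What is missing is a rule on which of them supports a statement about M3 and pill-taking.

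**Conclusion.** The point holds as a risk of bias in M3's favour, limited to M3 and interactions involving M3, and to device-based secondary outcomes in month 12, over months 1–12 and in the first half of months 1–24. Under assumed capture differences of 2 to 5 points, the spurious gap in mean adherence is about 1.6 to 4 points, with rejection of about 11% to 44%. The ≥90% outcome may be more sensitive. These figures show what is possible and do not estimate what will happen.

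The primary outcome, the viral load outcomes and refill-based retention are unaffected. Month-24 electronic adherence is less exposed, provided that it is observed in month 24. The carry-forward rule could otherwise fill it with a value from the call period.

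**What to change.** - For the M3 main effect and interactions involving M3, report electronic adherence in month 12 and over months 1–12 as a device-use (process) measure, and state the same reservation for months 1–24.
- Base the conclusion on M3 and adherence on a refill-based measure from the pharmacy data already collected, together with the planned viral suppression outcomes and month-24 electronic adherence. M2 is on in half the conditions at each level of M3 (Table 2), so M2's calls about refills do not unbalance the M3 main effect on that measure.
- For the month-24 M3 contrast, use observed month-24 data without carry-forward.
- Keep the planned analysis for the main effects of M1, M2, S1 and S2. Note that S1 and S2 may be started by the device record in M3-on conditions.

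The cost is one additional outcome definition and a change in how some secondary results are labelled. The main downside is that refill-based adherence is coarser than daily electronic data, and it shows possession, not ingestion.
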